### Interim analyses {21b}

The main analysis will be done after the completion of the 12-month follow-up. No interim analysis will be carried out before the study is completed.

### Methods for additional analyses (e.g. subgroup analyses) {20b}

To identify relevant influencing factors (confounders), multivariate regression models will be considered. Depending on the outcome variable, linear or logistic models will be implemented, and the patient’s age, sex, BMI, and respective baseline values will be used as covariates to adjust for.

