Currently, less clinical evidence is available regarding the role of barbed sutures used for anastomosis formation during robotic-assisted bariatric surgery, notwithstanding their usage is already widespread in this surgical intervention. In the authors’ view, barbed sutures have great advantages especially in robotic bariatric surgery, because in contrast to laparoscopic settings no assistance has to control, pull, and tighten the thread regularly, which simplifies the handling and construction of the anastomosis.

At the time, when the study protocol was prepared for the present study, a total of 14 clinical studies had been performed prospectively or retrospectively, either comparing conventional suture materials to barbed sutures [24–26] or reporting the outcome of barbed sutures [17, 28–36] for the construction of intestinal anastomosis during laparoscopic gastric surgery using either unidirectional or bidirectional mid-term or long-term barbed sutures. To our knowledge, the current RCT “BARGASTRO” will enrol the highest number of patients ever systematically analysed and published in robotic-assisted gastric bypass surgery. Furthermore, it will provide clinical data on evidence level Ib, due to its design. The present industry-initiated study is performed after the CE-mark of the suture material, and the participating hospital is the first user of the new unidirectional barbed suture in general surgery.

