## Methods: participants, interventions, and outcomes

### Study setting {9}

Patients will be recruited in a consecutive manner in one German Academic University Hospital (UKSH, Department of General, Visceral, Thoracic, Transplant and Paediatric Surgery, Kiel, Germany), which is familiar and well trained in the application of barbed and conventional threads as well as in robotic-assisted Roux-en-Y gastric bypass surgery. Approximately, 40,000 patients are treated in this hospital and 2300 within the Department of General, Visceral, Thoracic, Transplantation and Paediatric Surgery, and 80–100 robotic Roux-en-Y gastric bypasses are performed annually, revisional bariatric bypass procedures excluded (10–15 per year). The clinic has been selected to exclude a learning curve.

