### Sample size {14}

The sample size calculation is based on the primary endpoint “time to perform the GJA and JJA” to show superiority of a unidirectional barbed suture compared to a conventional suture material. Several studies have been published analysing both types of suture materials regarding this outcome parameter [6, 7]. The weighted group means and the weighted pooled standard deviations were calculated based on the results of the subset of four studies [24–27] providing suturing times to create the GJA. Considering 14.20 min to approximate the GJA in the barbed suture group compared to 16.10 min in the conventional group, a sample size of 71 patients in each suture group will have 80% power to detect a mean difference of −1.90 min assuming that the common standard deviation is 4.00 using a two-sample *t*-test with a 0.05 two-sided significance level. Including a drop-out rate of 5%, the sample size becomes up to 75 patients in each suture group, a total of 150 patients. The times to create the JJA are only reported in two studies [25, 27] with great differences. Therefore, to calculate the sample size for the current study, the time for the construction of the JJA was not taken into account. In addition, it was previously mentioned that the times for JJA formation did not differ between traditional and barbed sutures [6]. For sample size calculation, nQuery Advisor^®^7.0 was used.

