## Assignment of interventions: allocation

### Sequence generation {16a}

A statistician of the sponsor has prepared a computer-generated randomization list equally distributing both suture groups in a 1:1 ratio using different random block lengths unavailable to the clinic. The block sizes will not be disclosed, to ensure concealment. The randomization list is sealed and locked up at the sponsor site. Thus, the medical staff has no influence on the randomization. A stratification based on risk factors was not performed.

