## Data collection and management

### Plans for assessment and collection of outcomes {18a}

All participant data required based on the study protocol will be collected by the principal investigator or trained representatives and entered in a paper-based CRF provided by the sponsor.

Intraoperative documentation includes the following—the surgeon’s initials, surgeon’s position, randomization result (UBS or CS), and the use of antibiotic prophylaxis—and is performed for all study subjects.

In addition, the following parameters are mandatory and recorded and measured in all randomized patients during surgery:
Total operation durationEstimated blood lossIntraoperative blood transfusionSuturing time to create the gastro-jejunal anastomosisSuturing time to create the jejuno-jejunal anastomosisNumber of used threadsOutcome of the leak testHandling assessment of the suture materialDevice malfunctionsAdverse events

The EQ-5D-5L and BAROS self-assessment quality-of-life questionnaires will be filled in by the patients themselves. The completed CRFs and questionnaires will be securely stored in the principal investigator’s office, which is protected against unauthorized access.

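### The primary comparison of suturing time leaves out the operating surgeon, a recorded covariate that could narrow the confidence interval at almost no cost

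*Protocol article*

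**What the plan says.** The primary endpoint is the stopwatch time to sew both anastomoses (Protocol article, Primary outcome). Section {20a} compares the arms by an independent-samples t-test at the two-sided 5% level and sets the 95% CI against a minimum relevant difference of 1.9 min. It names no covariates.

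Section {20b} says that regression models will be considered, and that "age, sex, BMI, and respective baseline values will be used as covariates to adjust for". Surgeon is not listed. Section {16a} adds that "A stratification based on risk factors was not performed".

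Four other places bear on the surgeon:

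- Trial design {8} and the paragraph on suture handling under Outcomes {12} both speak of participating surgeons in the plural. Their number and case split are not given.
- Section {18a} lists among the items documented during surgery "the surgeon’s initials, surgeon’s position, randomization result (UBS or CS"), for all study subjects.
- Sections {11a} and {16b} place randomisation after the stapled anastomosis and before the enterotomy is sutured. The responsible surgeon brings the sealed envelope to theatre.
- Section {14} sizes the trial: "a sample size of 71 patients in each suture group will have 80% power to detect a mean difference of −1.90 min". The SD behind this is 4.00 min in both arms, and the test is two-sided at the 5% level.

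**The concern.** The outcome measures how quickly someone sews, so who is sewing is an obvious candidate predictor. The listed covariates describe only the patient. Variation between surgeons therefore stays in the error term of the t-test, and also in the residual of the supportive models as listed.

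In a randomised trial, a prognostic covariate fixed before allocation can be added to the model without threatening validity, and it removes its share of the variance. Here it is already collected. The plan fixes both the test and the covariate list, so this is a stated choice and not a detail left to an analysis plan. What is at stake is the width of the interval that {20a} proposes to read against 1.9 min, and the power to show superiority.

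**Working it through.** **Inputs from {14}:** difference 1.90 min, SD 4.00, two-sided α 0.05, 71 per arm, 5% dropout. **Assumptions:** the share R² of suturing-time variance due to surgeon (range 0.05 to 0.40) and four surgeons. Neither is in the documents.

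**1. The plan's own figure.** The standard error is 4.00 × √(2/71) = 0.671 min and the noncentrality is 1.90/0.671 = 2.83. With 140 degrees of freedom the noncentral t gives 80.3% power at 71 per arm and 79.7% at 70, so 71 reproduces. Then 71/0.95 = 74.7, rounded up to 75 per arm, 150 in total. The stated sample size is correct on its own inputs.

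**2. Adding surgeon.** The residual SD becomes 4.00 × √(1 − R²). Four surgeons use 3 further degrees of freedom: 142 − 2 − 3 = 137. The half-width is t(0.975; df) × residual SD × √(2/71).

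| R² (assumed) | Residual SD, min | Power at 71 per arm | 95% CI half-width, min | n per arm for 80% |
|---|---|---|---|---|
| 0 (unadjusted) | 4.00 | 80% | 1.33 | 71 |
| 0.05 | 3.90 | 82.2% | 1.29 | 68 |
| 0.10 | 3.79 | 84.2% | 1.26 | 64 |
| 0.20 | 3.58 | 88.1% | 1.19 | 57 |
| 0.30 | 3.35 | 91.9% | 1.11 | 50 |
| 0.40 | 3.10 | 95.2% | 1.03 | 43 |

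**3. Where chance imbalance sits.** The variance of the unadjusted difference is 16 × 2/71 = 0.451. At R² = 0.20 the surgeon part is 0.20 × 0.451 = 0.090 (SD 0.30 min) and the rest is 0.361. Across R² = 0.05 to 0.40 the surgeon part has an SD of 0.15 to 0.43 min, a 95% range of ±0.29 to ±0.83 min. This is a component of the 0.451, already counted in the t-test's standard error, and does not come on top of it.

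**4. Simulation check.** There were 4,000 trials per setting, with 71 per arm and four surgeons with case shares of 40, 30, 20 and 10%.

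| R² | Type I error, t-test | Type I error, adjusted | Power, t-test | Power, adjusted |
|---|---|---|---|---|
| 0.10 | 4.3% | 4.4% | 80.2% | 82.7% |
| 0.20 | 5.6% | 5.1% | 79.8% | 87.5% |
| 0.30 | 4.9% | 5.0% | 80.9% | 92.2% |

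The simulation error on power is about √(0.80 × 0.20/4000) = 0.6 percentage points. Both analyses hold their level. The adjusted power agrees broadly with the formula. It is lower at R² = 0.10 and 0.20, as expected, because the formula treats surgeons as balanced between arms.

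**The case against.** The strongest reply is that nothing stated is wrong. Under randomisation the unadjusted t-test is valid, it matches the method behind the sample size, and it delivers the planned 80% power if the SD is 4.00. That stands, and it limits the point to efficiency.

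The size of the gain is also unknown. A single centre, a standardised technique and trained surgeons ({8}, {9}) all point towards modest differences between operators. At 5 to 10% of variance, power rises only to 82 to 84%. That stands too, and is why the low end is shown.

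Section {16b} says who carries the envelope, not that this person sews both anastomoses. That the surgeon is fixed before allocation is a reasonable inference and not a statement in the text. The covariate needs a definition that makes it so.

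A change to the confirmatory test would also come late. Surgeons are unblinded, the sponsor receives each allocation by fax, and the Trial status section expects completion in the first quarter of 2026. An open-ended rule for pooling surgeons would add analytic freedom. This argues for a numeric rule and a fallback, not for leaving surgeon out of every model.

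Three stronger readings are tempting, and the documents do not support them:

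- **Bias from surgeon imbalance.** A reader might infer that the lack of stratification biases the result, or is a second harm beside lost precision. It is the same variance, already covered by the interval (step 3).
- **A contradicted learning-curve claim.** "The clinic has been selected to exclude a learning curve" may seem to clash with "the participating hospital is the first user of the new unidirectional barbed suture in general surgery". The first rests on experience with barbed and conventional threads and with robotic bypass, and the second concerns this one product. Both can be true. Slow early cases with the new suture are conjecture, and they would work against the superiority claim.
- **A missing baseline.** Suturing time has no baseline value, but the sentence in {20b} covers all outcomes and fits the quality-of-life measures.

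**Conclusion.** The point holds as one of precision. The plan leaves out of every listed model a covariate that is plausibly prognostic, recorded for all subjects and, on a reasonable reading, settled before allocation. The t-test remains valid and the sample size reproduces.

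The gain runs from about 2 power points and 0.04 min of half-width (R² 0.05) to about 15 points and 0.30 min (R² 0.40), and is nil if one surgeon does nearly all cases. It rests on the assumed variance share, on about four surgeons, and on SD 4.00. That SD was derived for the gastro-jejunal time alone, and the documents give none for the total time. That surgeon is the strongest predictor is a judgement, not a documented fact.

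**What to change.** Before database lock and before the statistician is unblinded:

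1. In {20a}, take the primary estimate from a linear model of total suturing time on arm and operating surgeon, with surgeon as a fixed effect. Report the adjusted mean difference with its 95% CI and test it at the two-sided 5% level.
2. Define operating surgeon as the person designated before the envelope is opened. Set a numeric rule for pooling surgeons with few cases, chosen without reference to allocation or outcome.
3. Keep the unadjusted t-test as a sensitivity analysis.
4. Add surgeon to the covariates in {20b} for suturing time.

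No new data are needed. The cost is a few degrees of freedom and, because the protocol itself fixes the test, an amendment with ethics approval under {25}. If the sponsor will not change the confirmatory test this late, the t-test can stay primary, with the surgeon-adjusted model as a pre-specified supportive analysis. A model with case number by arm, to look for a learning effect, is optional and exploratory.

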### Methods in analysis to handle protocol non-adherence and any statistical methods to handle missing data {20c}

All patients without a violation of the inclusion and exclusion criteria and who received the intended study treatment will be included in the primary analysis. Missing data/values will be analysed as such and will not be replaced by estimates. When reporting statistical distribution parameters, the number of non-missing values will be provided for transparency. Deviation from the study protocol will be assessed as protocol violations. If at least one inclusion or exclusion criterion is not fulfilled, the patient will be dropped out from the study.

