### Intervention description {11a}

All RYBG surgeries will be carried out as usual and according to the local standard using the da Vinci Xi Surgical System (Intuitive, Sunnyvale, CA, USA). Gastrojejunostomy (GJ) and jejuno-jejunostomy (JJ) in the Novosyn^®^ Group are performed in the same way as the GJ and JJ of the Symmcora^®^ Group. Randomization occurs after the creation of the side-to-side linear stapler anastomosis. Then, the enterotomy is closed by a continuous, running seromuscular suture. GJ is usually created with two threads starting from the corners. The JJ is usually with one thread. There is no difference regarding the procedure if Novosyn^®^ or Symmcora^®^ is used.

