### Criteria for discontinuing or modifying allocated interventions {11b}

Exit criteria will be as follows: (1) RYGB is not possible to be performed due to severe adhesions, (2) intraoperative decision to perform a gastric sleeve instead of a RYGB, and (3) intraoperative decision to modify the procedure due to visceral obesity, hepatomegaly, or adhesions.

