## Assignment of interventions: blinding

### Who will be blinded {17a}

Patients will be unaware of the type of suture material they receive to ensure a valid assessment of the postoperative outcome parameter, which they judge. It is impossible to blind the surgeon because, first, the suture type can be differentiated by configuration and feel, and second, the surgeon has to be aware of the suture type to perform the anastomosis. The statistician has no access to the eCRF or database. After data base closure, generation of the data export (performed by the data manager), and determination of the analysis population, the statistician responsible for the analysis will be unblinded.

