## Statistical methods

### Statistical methods for primary and secondary outcomes {20a}

The intention-to-treat principle will be applied for data analysis. A CONSORT diagram will be utilized to graphically display the eligibility, allocation, and follow-up course of the participants (**41**). Demographics, anamnesis, and baseline characteristics will be presented in a tabular form by treatment group. Continuous measures will be summarized by the number of non-missing observations, minimum, maximum, median, and mean with standard deviation, and categorical measures by absolute and relative frequencies.

The primary outcome measure is the suturing time to perform the GJA and JJA. The independent samples *t*-test with a two-sided significance level of 0.05 will be used for the comparison of treatment groups (UBS vs. CS). 95% CI will be provided to allow a quantitative evaluation of the treatment effect with respect to the minimum clinically relevant difference of 1.9 min. The secondary variables will be analysed descriptively.

The test regarding the primary variable is considered confirmatory; all other tests are explanatory. For the analysis of binary data, a chi-square test will be used; for nonparametric data, a *U*-test according to Wilcoxon–Mann–Whitney or to Kruskal–Wallis will be used; and a *t*-test or one-way ANOVA will be used for metric data, if a normal distribution is assumed. All statistical tests will be performed two-tailed with a pre-specified significance level of *α* = 5%. Two-sided 95% confidence intervals will be given, where appropriate.

The secondary outcomes include the following:
Pain (visual analogue scale, values from 0 to 100, 100—max. pain)Satisfaction (numeric scale values from 0 to 100, 100—best)EQ-5D-5L questionnaire: EQ index range from 1 best to 5 worse and EQ-VAS scale value (0–100—best).BAROS questionnaire, three sub-scores with a maximum of 3 points each (weight loss (% of excess), improvement of medical conditions and Quality of Life), and the total score with a maximum of 9 points (best).Length of hospital stay in daysHandling assessment of the suture material (different dimensions using a Likert scale with levels from 1 excellent to 5 worse).

The outcomes will be analysed descriptively and compared between suture groups and between visits, where appropriate.

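### The plan promises intention-to-treat, but its rule for the primary analysis admits only eligible patients who received the intended suture: a per-protocol population for the sole confirmatory test

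*Protocol article*

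**What the plan says.** Two sections of the protocol article define who enters the primary analysis.

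- Statistical methods {20a}: "The intention-to-treat principle will be applied for data analysis". The same section makes the t-test on suturing time the only confirmatory test.
- Section {20c}, on non-adherence and missing values, sets this rule: "All patients without a violation of the inclusion and exclusion criteria and who received the intended study treatment will be included in the primary analysis". It adds: "If at least one inclusion or exclusion criterion is not fulfilled, the patient will be dropped out from the study". On missing values: "Missing data/values will be analysed as such and will not be replaced by estimates".

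Four other sections bear on how the rule would work.

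- Intervention description {11a}: "Randomization occurs after the creation of the side-to-side linear stapler anastomosis". The concealment section {16b} places the opening of the envelope after stapling of the gastro-jejunal anastomosis (GJA) and before its enterotomy is sutured. The jejuno-jejunal anastomosis (JJA) is built later.
- Discontinuation criteria {11b}: one exit criterion is an "intraoperative decision to modify the procedure due to visceral obesity, hepatomegaly, or adhesions". No time limit relative to randomisation is given, and no rule for analysing such a patient.
- Blinding {17a}: "It is impossible to blind the surgeon because, first, the suture type can be differentiated by configuration and feel". The same section says that, after database closure, data export and "determination of the analysis population, the statistician responsible for the analysis will be unblinded".
- Outcome collection {18a}: both suturing times are mandatory in all randomised patients.

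**The concern.** Intention-to-treat means that every randomised patient is analysed in the allocated arm. The {20c} rule conditions on something that happens after allocation, namely whether the intended suture was actually used. That is a per-protocol definition, and it is attached to the primary analysis itself, not to a sensitivity analysis. As written, two statisticians could each follow the article and test different sets of patients.

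The endpoint is the time spent suturing, and the person suturing knows the allocation. If an operation that moves to another suture type, or is modified after the envelope is opened, tends to be longer or shorter than average, removing it changes that arm's mean for reasons connected with the suture. Randomisation no longer protects the comparison. The eligibility clause is less worrying: criteria fixed before randomisation, judged without knowledge of the arm, introduce little bias when used to exclude.

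**Working it through.** **1. The plan's own figure.** Inputs from Sample size {14}: difference 1.90 min (16.10 − 14.20), common SD 4.00, two-sided alpha 0.05, power 80%. Normal approximation: n = 2(1.960 + 0.842)² × 4.00²/1.90² = 69.6, so 70 per arm. With the exact noncentral t, power is 0.797 at 70 and 0.803 at 71, so the stated 71 is right. With 5% drop-out, 71/0.95 = 74.7, so 75 per arm and 150 in total. The sample size reproduces; the problem lies in the analysis population.

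**2. The two rules side by side.**

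| Randomised patient | Under {20a} | Under {20c} |
|---|---|---|
| Eligible, allocated suture used throughout | In | In |
| Failed thread replaced by one of the allocated type | In | In: intended treatment still received |
| Changed to another suture type | In, as allocated | Out of the primary analysis; not said to leave the study |
| Eligibility violation found later | In | Out, and dropped from the study |
| Procedure modified after the envelope is opened, no JJA time | In the set, but no total time | Not addressed; no imputation, so no value to test |

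The rules part company in the third and fourth rows, and neither settles the fifth. Sections {17b} (unblinded patients analysed as planned) and {18b} (data used up to discontinuation) do not resolve this.

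**3. Possible shift (assumed inputs).** Suppose k of 75 patients in one arm are removed and their times average m minutes above that arm's full mean. The remaining 75 − k patients then average k × m/(75 − k) below the full mean.

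| k | m (min) | Shift (min) | Share of 1.9 min |
|---|---|---|---|
| 1 | 8 | 8/74 = 0.11 | 6% |
| 2 | 8 | 16/73 = 0.22 | 12% |
| 4 | 4 | 16/71 = 0.23 | 12% |
| 4 | 8 | 32/71 = 0.45 | 24% |
| 4 | 12 | 48/71 = 0.68 | 36% |

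The article supplies neither k nor m. Its 5% drop-out allowance happens to equal 75 − 71 = 4 per arm, but it is not broken down by reason and does not forecast these exclusions.

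**4. Worst case for the test.** In a simulation (40,000 runs, normal times, SD 4, 75 per arm, no true difference), the k longest times were removed from the barbed arm only. The two-sided rejection rate was 0.049 at k = 0, 0.057 at k = 1, 0.071 at k = 2 and 0.116 at k = 4. At k = 4, 0.111 of the 0.116 favoured the barbed suture. Removing exactly the longest times from one arm is an extreme assumption, so these are upper illustrations.

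**5. Does the planned size support an as-randomised analysis?** With 75 per arm analysed as allocated, exact power is 0.824 at 1.9 min and SD 4. If a share c of one arm crosses over and takes the other arm's mean time, the difference becomes 1.9(1 − c). Power is then 0.816 at c = 1%, 0.808 at 2% and 0.784 at 5% (assumed range). These use the plan's inputs, which come from GJA times only.

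**The case against.** The strongest reply is that few patients would be affected. The envelope is opened just before suturing and the endpoint is recorded in the same operation, so there is little room for non-adherence. Section {11d} forbids other suture material, and section {16b} packs the allocated suture in appropriate numbers. Two of the three exit criteria (bypass not feasible, sleeve instead) would ordinarily be decided before randomisation. The analysis population is also fixed before the analysing statistician is unblinded. All of this stands and points to a modest likely effect. The last safeguard is only partial, however: it limits selection by the statistician but does not turn a treatment-received population into an intention-to-treat one.

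A reader might also infer more than the text supports:

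- That everyone outside the primary analysis leaves the study. Section {20c} says this only of eligibility violators.
- That safety follow-up of patients who already carry the suture stops. Section {22} intends to document all events to the 12-month examination. The drop-out wording is unclear for eligibility violators, but a loss of safety data is not established.
- That any thread rupture or needle detachment excludes the patient. Replacement with the same suture type leaves the intended treatment received and the long time in the analysis.
- That the bias must favour the barbed suture. Most of the device events listed in {22} can occur in either arm.
- That later non-compliance removes a patient, because noncompliance is an exclusion criterion. Eligibility is screened before surgery, and no section states such a rule.

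**Conclusion.** The contradiction is explicit, concerns the one confirmatory test and must be resolved before analysis. That conclusion rests on the text of {20a} and {20c} and needs no assumption about bias. Harm to the result is possible but not demonstrated: the number, direction and suturing times of any excluded patients are unknown, and exclusions are probably few. The 0.45 min illustration, about a quarter of the 1.9 min target, assumes four one-sided exclusions averaging 8 min above the arm mean. With one or two such exclusions the shift is 0.11 to 0.22 min.

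**What to change.** - In {20c}, define the primary analysis set as all randomised patients (envelope opened), analysed in the allocated arm with the recorded suturing times, whatever suture was used and whatever eligibility violation is found later.
- Keep the present {20c} population as a per-protocol sensitivity analysis.
- State how a randomised patient who exits under {11b} without a JJA time is handled, since no total time then exists. For example, count and report such patients by arm and add a sensitivity analysis.
- Reword the drop-out sentence for eligibility violators so that randomised patients who received a study suture clearly stay in the 12-month safety documentation of {22}, with the violation listed.

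The cost is wording in the protocol and the analysis plan. Section {18a} already requires both times in all randomised patients, so no new data collection is needed. The planned 150 patients keep power at about 80% or above if crossover in one arm is no more than about 2%, on the plan's own inputs.

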### Plans to promote participant retention and complete follow-up {18b}

The schedule of the study visits corresponds to the standardized aftercare scheme of the hospital. To promote the adhesion of the patients, they are reminded by the involved study nurse of the follow-up appointments by telephone call. The collected data set of patients discontinuing the study prematurely will be analysed until their discontinuation. The reason for discontinuation (e.g. withdrawal from the trial, lost to follow-up) will be recorded.

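### The 12-month quality-of-life comparisons use only patients with a value at that visit; a longitudinal model using the 30-day data already collected would be safer at almost no cost

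*Protocol article*

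**What the plan says.** Three statements in the protocol article together settle how late missing values are treated.

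- Section {20c}, on non-adherence and missing data: "Missing data/values will be analysed as such and will not be replaced by estimates". It adds a transparency measure: "When reporting statistical distribution parameters, the number of non-missing values will be provided for transparency".
- Section {18b}, on retention: "The collected data set of patients discontinuing the study prematurely will be analysed until their discontinuation". Reasons for discontinuation are recorded, and patients get telephone reminders of their visits.
- Section {20a}, on statistical methods: "The outcomes will be analysed descriptively and compared between suture groups and between visits, where appropriate". The tests named are chi-square, Wilcoxon–Mann–Whitney or Kruskal–Wallis, and t-test or one-way ANOVA.

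Section {20b} says linear or logistic regression will be considered to identify influencing factors, with age, sex, BMI and the respective baseline value as covariates. The Abstract gives the quality-of-life time points (before surgery, 30 days, 12 months) and plans comparisons between arms and over time. Section {14} allows 5% for drop-out. No expected 12-month attendance is given.

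**The concern.** Each named test uses whoever has a value at the visit concerned. For a patient who attends at 30 days but not at 12 months, the 30-day score is on file and predicts the missing one, yet it plays no part in the 12-month comparison. The result is unbiased for the arm means only if attendance is unrelated to recovery.

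The regression models in {20b} do not close the gap. They are optional, they omit the 30-day value, and they drop patients without a 12-month outcome. Nor does the 5% in {14} bound the problem, because it enlarges a sample sized on an intraoperative time.

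At stake are the late descriptive estimates. The Discussion counts the long-term follow-up among the features supporting the trial's evidence level, so these estimates are likely to be read and cited.

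**Working it through.** **1. The plan's own figure.** Inputs from {14}: difference 1.90 min, SD 4.00, two-sided alpha 0.05, power 80%. The normal approximation gives n = 2 × (1.960 + 0.842)² × (4.00/1.90)² = 69.6, so 70 per arm. The t-test calculation gives 70.55, so 71 per arm, with power 0.803. Then 71/0.95 = 74.7, so 75 per arm and 150 in total. The plan's figures reproduce. The 5% belongs to this calculation, which concerns suturing time. If 5% did apply at 12 months, 150 × 0.05 = 7.5 patients would lack a value.

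**2. Assumptions for the late scores (none is in the article).** A 0–100 score with SD 20 at both follow-up visits; correlation 0.6 between 30 days and 12 months; no true arm difference; log-odds of loss rising by b per SD worse 30-day score, with b = 0.69 (odds doubled), 1.0 or 1.5.

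**3. Formula.** Let d be the amount, in SD units, by which the 30-day mean of 12-month attenders exceeds that of all patients in the arm: d = E[X(1 − p(X))] / E[1 − p(X)], where X is standard normal, p(X) = 1/(1 + exp(−(a − bX))), and a is set to give the stated loss. Then:

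- bias of an arm's 12-month mean = 0.6 × 20 × d = 12d;
- bias of the between-arm difference = 12 × (d in arm 1 − d in arm 2).

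**4. Between-arm bias in points, by numerical integration.**

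| Loss in the two arms | b = 0.69 | b = 1.0 | b = 1.5 |
|---|---|---|---|
| Equal | 0 | 0 | 0 |
| 8% vs 2% | 0.48 | 0.65 | 0.86 |
| 15% vs 5% | 0.77 | 1.03 | 1.32 |
| 25% vs 10% | 1.12 | 1.47 | 1.86 |

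For example, at 15% vs 5% with b = 1.0: d = 0.1326 and 0.0471, and 12 × (0.1326 − 0.0471) = 1.03. The arm with more loss looks better.

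**5. Change from 30 days to 12 months within an arm.** The sign depends on which patients are compared.

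- All available patients at each visit: the 30-day mean is unaffected and the 12-month mean is too high by 12d, so improvement is overstated by 12d.
- Only patients with both values: the 30-day mean is too high by 20d and the 12-month mean by 12d, so improvement is understated by 8d.

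At 10% loss and b = 1.0, d = 0.0908. That is an overstatement of 1.1 points in the first case and an understatement of 0.7 in the second. Section {20a} does not say which set of patients is used.

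**6. What the remedy achieves.** In simulations under these assumptions (75 per arm, 4,000 trials per setting, b from 1.0 to 1.5), a maximum-likelihood estimate using the 30-day score left a between-arm bias of at most 0.13 points. Its standard error was about 3.4 to 3.6, within 0.1 of the available-case value.

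**7. A limit of the remedy.** If loss depends on the unseen 12-month score itself (odds doubled per SD), the available-case bias is about 0.8 points at 8% vs 2%, 1.3 at 15% vs 5% and 2.4 at 30% vs 10%. A model using the 30-day score cannot be relied on to remove all of this.

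**The case against.** **The outcomes are not confirmatory.** The article says "The secondary variables will be analysed descriptively" and "The test regarding the primary variable is considered confirmatory; all other tests are explanatory". This stands and sets the weight of the point. It does not make a biased descriptive estimate unbiased.

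**The rule forbids imputation only.** A likelihood model replaces no value, so it is compatible with {20c}, and an unseen analysis plan might contain one. The compatibility is real, and it means the fix can be added without reversing that sentence. But the article does more than stay silent. It states the missing-data rule, the use of data up to discontinuation, and the tests, and together these describe an available-case analysis.

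**Unequal loss is unlikely.** Patients are blinded, both arms follow the same aftercare schedule, and "they are reminded by the involved study nurse of the follow-up appointments by telephone call". This makes differential loss less likely without excluding it. A reader might infer that the arm comparison is biased whenever loss depends on recovery. The calculation does not support that, since with equal loss and the same link to recovery the bias is about zero.

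**Change over time.** A reader might infer that improvement is bound to be overstated. The documents do not support a direction, because paired comparison reverses the sign.

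**There is a model in the plan.** It would be wrong to say that no model is foreseen, given {20b}. Those models are not designed for missing follow-up and do not use the 30-day value.

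**Pain and satisfaction.** The text says they are compared over time, but their visits appear only in Fig. 1, which is not shown. The point is therefore firm for quality of life and conditional for these two.

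**Conclusion.** The point holds as a minor improvement. The article fixes available-case comparisons of 12-month quality of life and leaves unused a 30-day value that is on file for patients who attended then. If attendance depends on earlier recovery, arm means and change over time are biased, the latter in a direction the text does not determine. The between-arm difference is biased only if loss, or its link to recovery, differs by arm.

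The size is about 0.5 to 1.9 points on a 0–100 scale, roughly half a standard error at most (1.86/3.6 = 0.52). It rests on the assumed SD, correlation, strength of dependence and loss rates.

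It would be wrong to infer that the trial's main conclusion is at risk. The suturing time is recorded during surgery and does not depend on 12-month attendance.

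**What to change.** For the repeated quality-of-life scores (EQ-VAS and EQ-5D-5L index, plus pain and satisfaction if they are measured at both follow-up visits), state a likelihood-based longitudinal model:

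- terms for arm, visit and arm-by-visit, with the baseline value where it is collected;
- every randomised patient with at least one post-operative value included;
- the arm difference with its 95% confidence interval reported at 30 days and at 12 months.

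Keep the available-case table as a sensitivity analysis, and say whether its between-visit comparisons use all available or only paired patients. Report 12-month loss and its reasons by arm; the reasons are already being recorded.

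The cost is some wording and a little more analysis, with no new data and no change to the sample size. The model relies on data being missing at random given the observed values. That is a weaker assumption than the available-case comparison makes, but it is still an assumption and should be stated with the results.
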